#### Intervention Protocol

The planned intervention protocol is similar to that described for aim 2, for the rapid quality assessment as described in the *Protocol for Connected Care Model* section. We expect that the protocol will be improved through the iterative process we are using to optimize the implementation of our intervention. Full demographic variables relevant to SCI/D will be collected during the consent visit. The same surveys and structured interview will be completed after each visit by the intervention group participants and the therapists including assessment of usability (System Usability Survey [34]), acceptability (Unified Theory of Acceptance of Use of Technology [35,36]), feasibility (Feasibility of Intervention Measure [37]), and appropriateness [37] of the procedures.

#### Control Protocol

If participants are randomized into the control group, the standard of care protocol will be followed as used in the seating clinic. Demographic and additional variables will be collected from participants similar to those in the intervention group, and their clinical visit will be recorded for assessment of the visit.

#### General Statistical Methods

All tests are 2 sided, with a 0.05 type-1 error rate. Analysis will be conducted using SAS (SAS Institute) and R software (GNU Project). Mean and SD or median and IQR will be reported for all demographic, predictor, and outcome variables, as appropriate. For all outcome measures, the effect of relevant biological variables including sex, age, level of sensation, and pressure injury history will be assessed as covariates in the analysis. In addition, wheelchair type will be included as a covariate. Variables will be transformed as necessary to meet the appropriate distributional assumptions for modeling (eg, normality). For missing data, mixed models can be used to handle missing data naturally, so that all available data points may be analyzed, irrespective of whether the participant had some outcome data missing. However, analyses of data with multiple imputation for missing data may be attempted if the data are likely to be missing at random.

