#### Study Design

This single-site randomized controlled trial will use a modified intention-to-treat analysis. Randomization will be a stratified, block randomization with stratification based on wheelchair type (manual vs power) and current wound severity (no wound or stage 1 vs stage 2 or stage 3). The intervention group (26/52, 50%) will receive the connected care model that used AW-Shift in combination with telehealth. The control group (26/52, 50%) will receive the standard of care that uses telehealth when appropriate. The statistician will be masked to the group allocation information for the outcome measure analysis.

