#### Randomization

We will stratify based on wheelchair type (2 groups: power and manual), and current wound severity (2 groups: no wound or stage 1 and stage 2 or stage 3). We will block randomize in groups of 4. This randomization scheme will ensure distribution of important confounders between arms of the study. Furthermore, the blocking will ensure equal distribution of group assignment during the study.

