#### Primary Pilot Clinical Trial Effectiveness Outcomes

The primary effectiveness of the intervention will be captured via the collection of the following clinical outcomes: wound recurrence, early identification of wounds, wound healing, and hospital admission or readmission. The data for these metrics will be abstracted during the full year (365 days) after the study-related clinical visit for both the control and intervention group participants. Then, 2 independent therapist team members will abstract the medical records of each participant to search for the occurrence of an incident wound, stage at which wounds are identified, time frame of wound healing, and occurrence of a hospital admission or readmission directly related to a seating area pressure wound. Comparisons between groups for the primary outcome measures will be made using a 2-tailed *t* test. Additional comparisons will be made with regression and mixed effect models to explore the role of covariates on the study findings.

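### Randomisation is stratified by wheelchair type and current wound severity, but the primary t test uses neither and the covariate list names only wheelchair type, so precision is lost where wound severity is prognostic

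*Protocol article*

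**What the plan says.** All references are to the Protocol article.

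- **Study Design and Randomization (aim 3).** Allocation uses "stratification based on wheelchair type (manual vs power) and current wound severity (no wound or stage 1 vs stage 2 or stage 3"), which makes four strata. On block size: "We will block randomize in groups of 4". The stated purpose is that "This randomization scheme will ensure distribution of important confounders between arms of the study".
- **Primary Pilot Clinical Trial Effectiveness Outcomes.** The groups are compared on the primary outcomes (recurrence, early identification, healing, wound-related admission) with a two-tailed t test. Models come second: "Additional comparisons will be made with regression and mixed effect models to explore the role of covariates".
- **General Statistical Methods.** "All tests are 2 sided, with a 0.05 type-1 error rate". For all outcome measures, relevant biological variables including "sex, age, level of sensation, and pressure injury history will be assessed as covariates in the analysis". The next sentence reads: "In addition, wheelchair type will be included as a covariate". Current wound severity is not mentioned.
- **Sample Size (aim 3).** The plan is 26 per arm. The blocked design is listed among the steps taken to improve statistical power.

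**The concern.** A factor chosen for stratification is normally carried into the analysis. Stratified blocks keep the arms balanced on it, so differences between strata contribute almost nothing to the true sampling error of the treatment effect. A two-sample t test does not know this. Its pooled SD still contains the between-stratum variation, so the standard error it reports is larger than the real one.

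Here the primary test uses neither stratification factor, and the list for the additional models carries over only wheelchair type. The article treats both factors as important confounders, and the outcomes concern wounds, so some association between current wound severity and outcome is likely. What is at stake is precision: the section that justifies the sample size counts the blocking as a gain in power, and the planned test does not report that gain. The pilot's estimates are also meant to size the full trial.

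**Working it through.** **Is there a figure in the plan to reproduce?** Not for this point. The 25 per arm behind the sample size is a rule taken from cited guidance, and the article says it lacks the data to determine the power of this design. The check below does not depend on that rule.

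**Inputs from the article.** N = 52, 26 per arm; two-sided 5% level; four strata; blocks of 4; primary test unadjusted.

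**Assumptions, none in the article.** A normally distributed outcome observed in all 52 people, within-arm SD 1. R² is the share of within-arm variance explained by wound severity, varied from 0 to 0.4. Wheelchair type is given no effect. The two wound strata are of equal size.

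**Step 1: formula.** With balance on wound severity, the true variance of the difference in means is about (2/n)(1 − R²), while the t test estimates 2/n. So:

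- ratio of reported to true standard error = 1/√(1 − R²)
- actual two-sided error = 2[1 − Φ(1.96/√(1 − R²))]

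| R² | SE ratio | Actual error |
|---|---|---|
| 0 | 1.00 | 5.0% |
| 0.1 | 1.05 | 3.9% |
| 0.2 | 1.12 | 2.8% |
| 0.3 | 1.20 | 1.9% |
| 0.4 | 1.29 | 1.1% |

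**Step 2: simulation.** This used 8,000 trials per scenario, with permuted blocks of 4 within the four strata, so incomplete blocks are allowed for. It compared the t test with a linear model containing treatment and both stratification factors.

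| R² | Error, t test | Error, both factors | 95% CI width, t test | Width, both factors | Width ratio |
|---|---|---|---|---|---|
| 0 | 4.7% | 4.7% | 1.11 | 1.11 | 1.00 |
| 0.1 | 4.1% | 5.2% | 1.11 | 1.05 | 1.05 |
| 0.2 | 3.0% | 5.0% | 1.11 | 0.99 | 1.12 |
| 0.3 | 1.8% | 4.9% | 1.11 | 0.93 | 1.20 |
| 0.4 | 1.1% | 4.8% | 1.11 | 0.86 | 1.29 |

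Widths are in SD units; ratios come from the unrounded widths (for example 1.111/0.992 = 1.12). Formula and simulation agree. With R² = 0.2 and a 30/70 split of the wound strata, the results were nearly the same (error 3.0% against 5.0%; width 1.11 against 1.00).

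**Step 3: does wheelchair type alone help?** No, when wound severity is the prognostic factor. That model's mean width stays between 1.11 and 1.12, and its error falls from 4.1% at R² = 0.1 to 1.2% at R² = 0.4, as with the t test.

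**Step 4: power, as illustration.** At a standardised effect of 0.8 (an assumption), adjustment raises power from 82% to 85% at R² = 0.1, from 83% to 88% at 0.2, and from 85% to 95% at 0.4. At 0.2, the only effect size the article names, power is low either way: 9% against 13% at R² = 0.2.

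**Step 5: how large can R² be for admissions?** For a binary outcome with overall rate p and two equal strata, R² is greatest when every event falls in one stratum. The stratum rates are then 0 and 2p, and R² = p²/[p(1 − p)] = p/(1 − p). The Background's general rehospitalisation range of 11% to 20% is used here as an assumed rate:

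- p = 0.11: 0.11/0.89 = 0.12
- p = 0.20: 0.20/0.80 = 0.25

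These are ceilings. Rates of 25% and 5% in the two strata give 0.01/(0.15 × 0.85) = 0.08, an SE ratio of 1/√0.92 = 1.04.

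**The case against.** **The covariate list is open.** It is introduced as including certain variables, and exact model terms are often left to an analysis plan that is not shown. This stands as far as it goes: failing to name wound severity does not prove it will be left out of the additional models. It does not rescue the primary comparison, which the article itself fixes as an unadjusted t test. Pressure injury history is no substitute either, since eligibility already requires recurrent injury and history is not current stage.

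**The loss may be small.** This stands. At R² = 0 there is none, and at 0.1 the intervals are about 5% wider. The model in the working also fits some outcomes poorly. Healing is defined for prevalent wounds and stage at identification needs an identified wound, so neither is observed in all 52 people.

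**The balance is not wasted.** This also stands. Stratification makes the point estimate more precise even under a t test; unadjusted power at an effect of 0.8 rises from 82% to 85% as R² goes from 0.1 to 0.4. Only the reported standard error fails to reflect it.

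**A stronger reading to avoid.** A reader might infer that the models are over-parameterised, with five covariates in 52 people and few events for each parameter. The article does not support this. It says the covariates will be assessed and makes the models exploratory; nothing puts all five into one model. An events-per-parameter figure built on admissions alone would take a general rehospitalisation rate for a high-risk cohort and ignore the other outcomes, for which the Background cites recurrence rates as high as 80%.

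**Conclusion.** The point holds as a matter of efficiency. Two factors drive the randomisation, neither enters the primary test, and only one is named for the additional models. Where current wound severity is prognostic, the reported standard error and interval are too large and the test is conservative. It remains valid, and a reader should not infer an excess of false positives.

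The size cannot be fixed from the article. The range of no loss up to intervals 29% wider rests on the assumed R² of 0 to 0.4 and on a continuous outcome seen in everyone. For admissions, at the assumed rates and with equal strata, R² cannot exceed about 0.12 to 0.25 and is likely well below that. For healing and stage at identification the figures would differ. In a pilot that cannot state its own power, the practical harm is mainly less precise estimates for planning the full trial. It is worth correcting because the correction is nearly free.

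**What to change.** Make the primary between-group comparison stratified by, or adjusted for, both randomisation factors: wheelchair type and current wound severity in the two categories used for allocation. Use a model suited to each outcome (binary, time-based or ordered) in place of one t test for all. Add current wound severity beside wheelchair type in General Statistical Methods. Keep sex, age, level of sensation and pressure injury history in the exploratory models, as the primary outcomes section already plans.

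The cost is wording in the protocol and analysis plan. Both factors are recorded at randomisation, so no extra participants or data are needed. If wound severity proves unrelated to an outcome, adjustment costs almost nothing (mean interval width 1.11 SD either way at R² = 0).

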#### Primary Pilot Clinical Trial Effectiveness Outcomes

The primary effectiveness of the intervention will be captured via the collection of the following clinical outcomes: wound recurrence, early identification of wounds, wound healing, and hospital admission or readmission. The data for these metrics will be abstracted during the full year (365 days) after the study-related clinical visit for both the control and intervention group participants. Then, 2 independent therapist team members will abstract the medical records of each participant to search for the occurrence of an incident wound, stage at which wounds are identified, time frame of wound healing, and occurrence of a hospital admission or readmission directly related to a seating area pressure wound. Comparisons between groups for the primary outcome measures will be made using a 2-tailed *t* test. Additional comparisons will be made with regression and mixed effect models to explore the role of covariates on the study findings.

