#### Home and Community Use of the AW-Shift System

Participants will use the system for an estimated 2 weeks before their clinical visit. Participants will have easy access via phone; secure, web-based format; email; and SMS text message for technical and therapy support. A potential prescription could include (but not be limited to) mapping the variety of surfaces the participant sits on in the home and community (the system can be used on any surface), completion of daily weight shift protocols to assess participant positioning on their cushion, measurement of how the participant performs weight shifts with and without reminders provided by AW-Shift, and measurement of the effectiveness of the weight shifts to offload pressure.

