#### Study Procedures

For initiation and administration of the intervention, the following procedures will be followed:

Project initiation: The project will be initiated following a study initiation checklist by the PI and local site investigators.Staff training for the intervention: Staff will be instructed about how to use the AW-Shift system, view and use the mHealth report, and administer data collection elements as is appropriate for each study role. Data collection procedures will be standardized and tested for consistency across study team members.Participant recruitment: Recruitment and enrollment during year 2 will occur primarily through clinical staff in collaboration with the study coordinator.Intervention study period: The intervention will begin with 2 weeks of AW-Shift use at home by the patient with SCI/D, followed by a web-based clinical visit with a seating clinic therapist. Before mailing AW-Shift to participants, individualized tasks will be assigned by the seating specialist. The tasks are meant to inform the seating assessment process during the clinical visit. Participants and seating specialists will complete surveys after the seating clinic visit and participate in a guided interview.

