#### Potential Limitations and Alternative Strategies

In addition to the potential limitation described for aim 2, aim 3 has the added potential of loss to follow-up. As the long-term follow-up data are passively extracted from the medical record, we acknowledged that patients may seek care outside the original health system they were recruited from. In addition, for participants who have data that we cannot access, we will seek the approval of the participant to access their medical records from other medical systems.

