#### Potential Risks

There is the potential for skin irritation from sitting on a pressure mat for long periods. Participants may sit on the pressure mat throughout the day or may simply use it for short periods while performing their prescribed activities. Participants will be instructed to do a skin check every day and log their findings.

Participants are instructed to call the study coordinator if a new area of skin breakdown or wound occurs while they are using the pressure mat or if a current wound worsens. The participant will be asked to remove the mat until the skin breakdown or wound resolves. If the area does not resolve and worsens further, the participant will again contact the study coordinator and will then be referred to their typical clinical care provider in the case of a potential, new-onset incidence of pressure ulcers of stage 3 or 4. Initializing and deploying the AW-Shift system will require performing transfers and weight shifts. Transfers always have some risk of injury or fall, and the participant will be advised to transfer in their usual manner. Weight shifts will include typical functional movements, such as leaning forward and sideways, but participants will be instructed to only perform weight shifts with which they are comfortable. Risks from transferring on their own while the sensors are on the wheelchair are no different than transferring without the sensors present.

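### The 365-day primary outcome window opens at the study clinic visit, after randomization and after the intervention arm's device period, so pre-visit wounds are not counted as incident and people without a visit have no window

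*Protocol article*

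**What the plan says.** **Outcome window.** The section Primary Pilot Clinical Trial Effectiveness Outcomes covers wound recurrence, early identification, healing and admissions. It states: "The data for these metrics will be abstracted during the full year (365 days) after the study-related clinical visit", and applies this "for both the control and intervention group participants".

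**Intervention path.** Study Procedures (aim 3) states: "The intervention will begin with 2 weeks of AW-Shift use at home by the patient with SCI/D, followed by a web-based clinical visit". The aim 2 protocol, which Intervention Protocol describes as similar, gives the length only as an estimate: "Participants will use the system for an estimated 2 weeks before their clinical visit". It also places shipping and a set-up session before the home period.

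**Control path.** Control Protocol assigns the seating clinic's standard of care. It has no device period and gives no interval from randomization to the visit.

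**Follow-up in the aims.** Aim 3, under Overall Objective and Specific Aims, has patients randomized to one of the two models with a follow-up of 1 year.

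**Analysis set.** Study Design (aim 3) states: "This single-site randomized controlled trial will use a modified intention-to-treat analysis". The article does not say what the modification is.

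**Skin events during device use.** Potential Risks states: "There is the potential for skin irritation from sitting on a pressure mat for long periods". The same section has participants check their skin daily, log the findings and call the coordinator about new or worsening breakdown while using the mat. Skin Safety (aim 2, carried into aim 3 by its limitations section) adds tracking during the study.

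**The concern.** In a randomized comparison, outcome counting should start at randomization, because the groups are known to be comparable only at that moment. Here it starts at a later event that the two arms reach by different routes. One route includes part of the assigned treatment, and that part carries a skin risk which the article itself names.

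Three things follow from the text:

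- A wound that first appears before the visit is not an incident wound within the window, and the stage at which it was found does not enter early identification.
- If that wound is still open at the visit, it may be taken as a prevalent case for the healing outcome, although the randomization strata use wound severity at randomization.
- A participant who never has the visit has no day 0, so the plan does not say over which 365 days that person's record is to be read. The mixed-model and imputation text under General Statistical Methods does not supply a start date.

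According to Sample Size (aim 3), the pilot's results will be used to power the full trial. An unclear time origin would carry over into that planning.

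**Working it through.** The plan gives no figure on this point to reproduce. The check sets the passages side by side and then sizes the uncounted period.

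**Step 1: the order of events.**

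| | Intervention | Control |
|---|---|---|
| After randomization | Shipping, set-up, 2 weeks of device use | Standard care |
| Time to visit | 2 weeks of use plus an unstated lead time | Not stated |
| Outcome window | 365 days from visit | 365 days from visit |
| Follow-up as worded in Aim 3 | 1 year, tied to randomization | 1 year, tied to randomization |

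Both arms get the same length of window. What differs is how day 0 is reached, and day 0 is not randomization in either arm.

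**Step 2: share of time left out.** Counting only the stated 14 days: 14 / (14 + 365) = 14/379 = 3.7% of the span from device start to end of window.

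**Step 3: expected intervention participants with a new wound in those 14 days.**

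Inputs:
- 26 per arm (Sample Size, aim 3).
- Incidence of 25% to 38% (Background). No time base is given; reading it as annual is an assumption.
- Rates implied by the eligibility questions in Study Population (aim 3): roughly one every two years (0.5 per year), or at least one a year (1 per year as the floor). The third question, on near-constant sores, has no rate; 2 per year is an assumption.

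Formulas, at constant hazard: rate r = −ln(1 − p) where an annual risk p is given; 14-day risk q = 1 − exp(−r × 14/365); expected number = 26q; chance of at least one = 1 − (1 − q)^26.

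| Input | r per year | q | 26q | At least one |
|---|---|---|---|---|
| p = 25% | 0.288 | 1.10% | 0.29 | 25% |
| p = 38% | 0.478 | 1.82% | 0.47 | 38% |
| r = 0.5 | 0.5 | 1.90% | 0.49 | 39% |
| r = 1 | 1 | 3.76% | 0.98 | 63% |
| r = 2 (assumed) | 2 | 7.38% | 1.92 | 86% |

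For comparison, the number of 26 with a wound within a year is 26 × 0.25 = 6.5 at the lowest input, and 26 × (1 − e^−1) = 16.4 at one wound per year. The direct loss is small against either. These are gross counts in one arm: control wounds before the visit are also uncounted and cannot be subtracted, because the control interval is not given.

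**Step 4: people who never have the visit.** Each one is 1/26 = 3.8% of an arm. If 5% to 20% of an arm never reach it (assumption), that is 1.3 to 5.2 people. As an illustration only, suppose:
- a fraction d of the intervention arm has no visit and is left out;
- their risk is k times the arm average p;
- no controls are lost, and there is no true effect.

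The observed intervention risk is then (p − d·k·p)/(1 − d).

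- d = 0.10, k = 1.25, p = 0.38: (0.38 − 0.0475)/0.90 = 0.369, a fall of 1.1 points.
- d = 0.20, k = 1.5, p = 0.63: (0.63 − 0.189)/0.80 = 0.551, a fall of 7.9 points.

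The range of about 1 to 8 points rests wholly on these assumptions. Similar loss of similar people in the control arm would cancel it.

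**The case against.** **There is a reason for anchoring at the visit.** The home tasks exist to inform the seating assessment, and the trial asks whether that adds value to clinical care. A visit anchor gives each arm a full year after that care. This stands as a reason to keep the window as a sensitivity analysis. It does not make the visit a randomized time origin.

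**Device-period skin harm is not hidden.** A reader might infer that it is. The documents do not support that: wounds during mat use are logged, reported to the coordinator and monitored for safety. What is missing is their place in the comparison between arms, since this monitoring is written for device users.

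**Pre-visit wounds are not lost to every outcome.** One still open at the visit can enter through healing, and a related admission within the following 365 days is counted. The loss concerns incidence and stage at identification.

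**One-arm exclusion is not written anywhere.** A reader might take *modified* intention-to-treat to mean that intervention dropouts are removed. The article does not say so, the definition may stand in an analysis plan that is not shown, and a control without a visit lacks a window just as much.

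**Direction is not shown.** It is tempting to say that the design favours the intervention. If controls wait as long or longer for their visit, any bias could vanish or reverse.

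**This is a 52-person pilot, and the numbers are small.** That is right, and it limits the weight of the point.

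**Conclusion.** The point holds as one about the time origin. As written, the primary outcomes are counted from a post-randomization visit that the arms reach by different paths, in conflict with the most natural reading of the 1-year follow-up in Aim 3. Anyone without a visit has no defined window.

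The direct effect of the 2 weeks is about 0.3 to 1 of 26 intervention participants. This assumes constant hazard, the Background incidence read as annual, and a rate of up to one wound a year from the eligibility questions. An assumed 2 per year gives about 1.9. Longer pre-visit gaps, or the 80% recurrence figure (the highest reported, with no time base) used as an annual risk, would give larger counts, but the article supports neither. Loss of people before the visit could matter more, but its size is not known from the article. The direction of any bias cannot be determined.

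This is an inexpensive improvement that protects the randomized comparison. It is not evidence of concealed harm or of a result tilted towards the device.

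**What to change.** - In Primary Pilot Clinical Trial Effectiveness Outcomes, start the 365-day abstraction at randomization in both arms, for every randomized participant, whether or not set-up or the visit took place.
- Reconcile three places with this: the follow-up wording in Aim 3, the analysis-set wording in Study Design, and the window itself. The analysis set should be worded so that a missed visit does not remove a participant from the primary comparison.
- Report wounds between randomization and visit by arm, together with the time from randomization to visit in each arm.
- Keep the visit-anchored 365 days as a sensitivity analysis.

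**Cost.** Mainly wording. The limitations section for aim 3 notes that "the long-term follow-up data are passively extracted from the medical record", so an earlier start needs no added patient contact, only a somewhat longer stretch of record to cover both windows. Ethical Considerations says that approval for aims 2 and 3 is still to be sought, so the change can go into that submission. The downside is slight dilution, because time before the visit-based part of care is included.

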#### Aim 3: Pragmatic, Hybrid Implementation Trial (Implement the Connected Care Solution via a Pilot, Pragmatic Trial Comparing Clinical Outcomes Between the Connected Care Model and Standard Practice)

Patients identified as having high risk for pressure injury recurrence will be randomized to either the connected care model (Figure 2) or the standard model of care for a 1-year follow-up time frame. Our implementation outcomes include important stakeholders’ assessment of feasibility, acceptability, appropriateness, costs, and improved monitoring. Our pilot effectiveness outcomes are rate of wound healing for prevalent cases, incidence and recurrence of pressure injuries, early identification of wounds, and hospital admissions or readmissions.

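### The 365-day outcome window opens at the clinic visit, so new wounds during the post-randomisation AW-Shift home-use phase fall outside the incidence and early-identification outcomes

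*Protocol article*

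**What the plan says.** Under Primary Pilot Clinical Trial Effectiveness Outcomes, the Protocol article names wound recurrence, early identification of wounds, wound healing and hospital admission or readmission. The data for all of them are "abstracted during the full year (365 days) after the study-related clinical visit for both the control and intervention group participants".

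Study Procedures (aim 3) gives the order of events in the intervention arm: "The intervention will begin with 2 weeks of AW-Shift use at home by the patient with SCI/D, followed by a web-based clinical visit". The aim 2 section Home and Community Use of the AW-Shift System, which aim 3 largely adopts, agrees: "Participants will use the system for an estimated 2 weeks before their clinical visit". Before that, tasks are assigned and the device is mailed and set up. For controls, Control Protocol says only that "the standard of care protocol will be followed as used in the seating clinic".

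The aim 3 summary says that high-risk patients "will be randomized to either the connected care model (Figure 2) or the standard model of care for a 1-year follow-up time frame". It gives no date from which that year runs.

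Potential Risks acknowledges the device phase as a time of skin risk: "There is the potential for skin irritation from sitting on a pressure mat for long periods". It asks for a logged skin check every day and tells participants to "call the study coordinator if a new area of skin breakdown or wound occurs while they are using the pressure mat".

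**The concern.** Randomisation protects a comparison from the moment of allocation onwards. Here the outcome clock starts later, at an event that in one arm is preceded by what the protocol itself calls the beginning of the intervention. The time left out is time on the device, with daily skin inspection, in one arm only.

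Two opposite distortions follow. A wound that the mat provokes in those weeks is not an incident wound in the effectiveness comparison, which flatters the intervention. A wound caught early because of home monitoring or the daily checks earns no credit under early identification, which works against it. In addition, a participant who is randomised but never attends the visit has no day 0 and cannot be placed in the window at all. Such losses could differ by arm, because only one arm has a device phase to complete first.

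**Working it through.** **Timing, from the text**

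1. Only the intervention group receives AW-Shift (aim 3 Study Design, Control Protocol), so home use must follow randomisation.
2. Home use, about 14 days, precedes the visit (Study Procedures, Home and Community Use).
3. The window opens after the visit (Primary Effectiveness Outcomes).
4. No section carries the outcomes back to randomisation. At least 14 post-randomisation days on the device are therefore outside the window in the intervention arm.

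**What happens to a wound first seen in those days**

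| Outcome | Effect of the stated window |
|---|---|
| Incidence or recurrence | Not counted as a new wound |
| Early identification | Stage at first identification falls outside the window |
| Healing | Unclear: Randomization records wound severity for stratification, but nothing says whether that status or the status at the visit defines a prevalent wound |
| Admission or readmission | Counted if the admission falls in the 365 days, whenever the wound arose |

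**Size**

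The plan gives no figure to reproduce here; the window start is a design choice. Inputs are 26 participants per arm (aim 3 Sample Size), 14 days (Home and Community Use), and the introduction's incidence of 25% to 38% and recurrence of up to 80%. The article states no time base for these rates. I take them as annual risks p, which is an assumption, with a constant hazard.

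- Share of time left out: 14 / (14 + 365) = 14 / 379 = 3.7%.
- Hazard: h = −ln(1 − p) / 365. Risk of a first wound in 14 days: q = 1 − exp(−14h).
- Expected intervention participants affected: 26q. Chance of at least one: 1 − (1 − q)^26.
- Participants with a wound in the gap and none in the following 365 days: 26 × q × (1 − p).

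| p (assumed annual) | q | 26q | At least one of 26 | Gap wound and none in the window |
|---|---|---|---|---|
| 25% | 1.10% | 0.29 | 25% | 26 × 0.0110 × 0.75 = 0.21 |
| 38% | 1.82% | 0.47 | 38% | 26 × 0.0182 × 0.62 = 0.29 |
| 80% | 5.99% | 1.56 | 80% | 26 × 0.0599 × 0.20 = 0.31 |

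These use background risk only; skin harm from the mat would add to them. Mailing and set-up lengthen the gap by an unstated amount. If the visit came 28 days after randomisation (assumed), 26q would be 0.57, 0.94 and 3.02.

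**The case against.** The visit is a defensible anchor. It is the same event with the same window length in both arms, and the home data exist to inform it, so the weeks before it precede any visit-based change in care. Skin harm on the mat is not lost to the trial: there are daily logged checks, calls to the coordinator, skin-safety tracking (stated under aim 2 and carried into aim 3) and urgent reporting to the principal investigator and the review board. The numbers are small, and a participant with a wound in the gap will often have another in the window. This is also a 52-person pilot.

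Much of that stands, and it rules out several stronger readings that a reader might infer:

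- That a device-related wound cannot count in any primary outcome. It can, through a later admission, and possibly through healing.
- That such wounds are re-labelled as baseline wounds. No section says so; the article is silent on which date defines prevalence.
- That the outcome section contradicts the 1-year follow-up in the aim 3 summary. The summary gives no start point.
- That the interval from randomisation to visit is longer in the intervention arm. No control waiting time is given, and participants in both arms must have had, or be scheduled for, a seating clinic visit. Only the device phase is shown to be specific to one arm.
- That a large share of wounds is lost. That needs a much longer gap or higher wound rates than the documents give.

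What does not stand is that equal wording makes the window neutral. The exposure and skin surveillance before day 0 depend on allocation. Safety tracking does not feed the incidence or early-identification comparison. An analysis plan may define the modified intention-to-treat set, but that would not supply a window start for someone without a visit.

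**Conclusion.** The point holds in a limited form. As stated, the window omits about 14 post-randomisation days on the device in one arm (3.7% of 379). New wounds arising or first identified then are outside incidence and early identification, and participants without a visit have no day 0. The direction of bias is not fixed.

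With the introduction's rates read as annual, about 0.3 to 1.6 of 26 intervention participants would have a first wound in that phase. Only about 0.2 to 0.3 would have their yes/no wound status over the whole period changed by the omission. The effect falls mainly on which wound, at which stage, is counted as the first identified. Both ranges rest on the assumed time base and a constant hazard; gaps beyond 14 days are assumptions. With 26 per arm, one or two wounds can shift a pilot estimate, and the pilot is meant to power the full trial. This supports a cheap improvement to the definition and not a must-fix error.

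**What to change.** In Primary Pilot Clinical Trial Effectiveness Outcomes:

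- Start the window at randomisation in both arms, from day 0 to day 365.
- Define prevalent wounds and their stage by the status recorded at randomisation, which is already collected for stratification.
- Count a wound first identified between randomisation and the visit as incident, at the stage found then.
- Report days from randomisation to visit by arm.
- Keep the 365 days after the visit as a sensitivity analysis.

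The cost is wording in the protocol and abstraction form. To serve both windows, chart review runs to 365 days after the visit, about 379 days from randomisation with a 14-day gap. The downside is slight dilution of any effect of the visit, since 14/365 = 3.8% or more of the main window precedes it. Review-board approval for aim 3 had still to be sought when the article was written, so the change could be made at that step.
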